### Statistical analysis

2.6

The analyses will be performed using SPSS 22.0.0 (SPSS Inc, Chicago, IL). Frequencies and descriptive statistics will be used for patients’ demographic presentation, while means and standard deviations will be calculated for the continuous variables and group differences will be analyzed by using Pearson *χ*^2^test for categorical variables. Kolmogorov–Smirnov test will be applied to check the distribution of data. Independent *t* test will be used in case of normally distributed data, whereas Mann–Whitney *U* test for non-normal distributions. *P* < .05 will be considered significant for all analyses.

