### Random allocation

2.3

Before starting the study, a randomization list is produced using software-generated randomized numbers; the randomization depends on random blocks of 10. Eligible participants are divided into 3 groups according to completely randomized design: combined group (music therapy + Tai Chi), music therapy alone group and Tai Chi alone group (Fig. 1). The program duration is 12 months. Participants are enrolled by the research assistant. After baseline examination, all patients will be given a full explanation of the treatment protocol and will be required to sign a written informed consent for study participation and for the publication of the results. All the data collectors, statistical analysts, as well as result assessors are not aware of grouping assignment (Fig. 1).

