### Intervention and control protocols

2.4

The music therapy group is provided by a trained music therapist, who is registered with the appropriate professional association or registration body in his or her country and should also be skilled as a musician. To facilitate individual relationship-building, the music therapist will offer each resident an initial 20 minutes assessment with the aim of determining their musical preferences and starting to build individual rapport. The music therapist will also use other sources to determine the participants’ musical biography, cultural background, history, personal strengths, resources and disabilities, and any other information that could be useful to bring into music therapy sessions.

Tai Chi is taught as a 24-form Yang style; instruction is given 5 days per week for 1 h for 12 weeks. The Tai Chi group is led by an experienced practitioner who will demonstrate a set of slow, nonstrenuous movements coordinated with deep breathing. Participants are taught traditional Sun and Yang styles of Tai Chi. Instructors will take participants through warm-up exercises for 5 minutes, Tai Chi movements and form for 20 minutes and cool down exercises for 5 minutes. At the end of the 12-week period, participants are encouraged to continue Tai Chi, either alone or via a community group; however, no assistance is provided by the investigators during this period.

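### Tai Chi appears to be taught in shared classes, yet the tests named for continuous data assume independent participants; if classes or instructors are arm-specific, combined versus Tai Chi alone rejects too often

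*Protocol article*

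**What the plan says.** Section 2.3 (Random allocation) randomises individuals to combined therapy, music alone or Tai Chi alone. Tai Chi is therefore part of two arms. No separate form of Tai Chi is described for the combined arm.

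Section 2.4 (Intervention and control protocols) describes the teaching: "instruction is given 5 days per week for 1 h for 12 weeks". It adds: "The Tai Chi group is led by an experienced practitioner who will demonstrate a set of slow, nonstrenuous movements coordinated with deep breathing". The session has a fixed running order: "Instructors will take participants through warm-up exercises for 5 minutes, Tai Chi movements and form for 20 minutes and cool down exercises for 5 minutes". For music it says only that "The music therapy group is provided by a trained music therapist", with an individual assessment of 20 minutes at the start. It does not say whether the later music sessions are individual or in groups.

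Section 2.6 (Statistical analysis) names two tests for continuous data. The independent t "test will be used in case of normally distributed data", and the Mann-Whitney U test is used otherwise. The significance level is .05 throughout. The section mentions no class, instructor or therapist term.

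**The concern.** People who attend the same class under the same instructor tend to have more similar outcomes than people who do not. Five days a week for 12 weeks is 5 × 12 = 60 taught sessions, which leaves ample room for a class or instructor effect. The t test and the Mann-Whitney test count each participant as a separate piece of information. When classes are nested within arms, the difference between arm means also carries the variation between classes, and these tests leave it out of the standard error.

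The comparison most exposed is combined versus Tai Chi alone. The Introduction and Discussion ask whether the combination is more effective than either treatment given alone, and this is one of the two contrasts that answer that question. The practical risk is a claim of added benefit that reflects better classes or instructors in one arm.

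**Working it through.** **Inputs from the article.** Individual randomisation to three arms (2.3); led Tai Chi in two of them (2.3 and 2.4); independent t or Mann-Whitney test, significance level .05 (2.6). Sidedness is not stated and is taken as two-sided.

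**Inputs that are assumptions.** Class size m and ICC. The article gives neither, nor the number of classes, nor a sample size. There is thus no stated figure to reproduce, and the result is shown over a range.

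**Case 1: classes separate by arm, combined versus Tai Chi alone.** Both arms are clustered.

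- Design effect: DE = 1 + (m − 1) × ICC
- True standard error divided by the standard error that the test uses: √DE
- True two-sided error at nominal 5%: 2 × (1 − Φ(1.96 / √DE))

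For m = 10:

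- ICC 0.02: DE = 1 + 9 × 0.02 = 1.18; √DE = 1.086; 1.96 / 1.086 = 1.80; error 7.1%
- ICC 0.05: DE = 1 + 9 × 0.05 = 1.45; √DE = 1.204; 1.96 / 1.204 = 1.63; error 10.4%
- ICC 0.10: DE = 1 + 9 × 0.10 = 1.90; √DE = 1.378; 1.96 / 1.378 = 1.42; error 15.5%

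Other class sizes:

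| Class size | ICC 0.02 | ICC 0.05 | ICC 0.10 |
|---|---|---|---|
| 5 | 5.9% | 7.4% | 9.8% |
| 10 | 7.1% | 10.4% | 15.5% |
| 20 | 9.5% | 16.1% | 25.0% |

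Simulating the independent t test with 3 classes of 10 per arm (20,000 runs) gave 10.6% at ICC 0.05 and 16.4% at ICC 0.10. A separate set of 6,000 runs gave 7.4% to 7.5% at ICC 0.02 with 3 or 5 classes of 10. Both agree with the formula.

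A single class of 30 per arm at ICC 0.05 gave 21.8%. In that layout the class effect is fully confounded with treatment, and no analysis can separate the two.

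**Case 2: the two Tai Chi arms share classes.** The class effect falls on both arms and cancels in their difference, but it remains in the pooled standard deviation. The unadjusted standard error is then slightly too large. Simulated error was 4.3% to 5.4%.

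**Case 3: comparisons with music.** The variance on the music side depends on whether sessions are individual or in groups and on how many therapists there are. Section 2.4 gives none of this, so no figure is offered.

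**The case against.** The strongest objection is that class teaching is never stated. In this article the word group is also the arm label, as in section 2.3 and the column heads of Table 1, and section 2.4 uses the same construction for music. No class, class size or number of classes appears. This stands: shared classes are a strong inference from a leader demonstrating movements and instructors taking participants through a timed routine. Even with one-to-one teaching, clustering by instructor would remain possible.

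Three stronger readings are tempting, and the article supports none of them.

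- A reader might infer that only the Tai Chi side is clustered in a comparison with music, and compute an error rate on that basis. Section 2.4 leaves the format of the music sessions open, and clustering by therapist is possible in both arms that receive music.
- A reader might infer that the planned tests are certainly anti-conservative. That depends on whether classes or instructors are specific to an arm, which the article does not say.
- A reader might take one of the error rates as the size of the problem in this trial. Each rests on an assumed class size and ICC, and with small classes and a low ICC the inflation is slight.

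It can also be said that a condensed article leaves model details to a full plan, and that the sentence on the t and Mann-Whitney tests names no outcome or contrast. Both are fair. The point does not rest on a missing detail, however. The article itself names the tests, they are the only ones it gives for continuous data, and their independence assumption is doubtful for the delivery it describes.

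Finally, a model with a class effect may have little to work with. If there are few classes per arm the degrees of freedom are few, and with one class per arm the class effect cannot be estimated. This stands and is counted in the cost of the fix.

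**Conclusion.** The concern holds conditionally. If Tai Chi classes or instructors are specific to an arm, the tests in section 2.6 understate the standard error, chiefly for combined versus Tai Chi alone. With assumed classes of 10, the two-sided error is about 7%, 10% or 16% at an ICC of 0.02, 0.05 or 0.10. Over assumed classes of 5 to 20 and the same ICCs it runs from about 6% to 25%. If the two arms share classes, the planned test is about nominal or slightly conservative for that contrast. For comparisons with music, neither the size nor the pattern of clustering can be settled from the article. These results rest on reading the teaching as shared classes, on Tai Chi being delivered in the combined arm as in the Tai Chi arm, and on the assumed class sizes and ICCs.

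**What to change.** 1. Record for every participant the Tai Chi class and instructor, and the music therapist or music group. Participants in the combined arm need both. Capture this as treatment is delivered, since it may be hard to reconstruct later.
2. In section 2.6, replace the t and Mann-Whitney tests on the outcome scores with a linear mixed model, which the planned SPSS can fit: arm and baseline score as fixed effects, a random effect for the delivery cluster, and small-sample degrees of freedom. Code a participant as a cluster of one only if treated individually. The baseline score does not deal with clustering; it is there because the model for the scores is being specified and it can recover some precision.
3. State whether the two Tai Chi arms share classes or instructors. If an arm has only one class or instructor, say that its effect cannot be separated from treatment.

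Cost: one or two data fields and a change of analysis wording. Confidence intervals will be wider, noticeably so with few classes. For example, with an assumed 3 classes per arm and degrees of freedom taken at class level, 2 × 3 − 2 = 4, the critical value is 2.78 rather than about 2.0. Intervals are then about 40% wider (2.78 / 2.0 = 1.39), even if classes do not differ.

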### Outcomes

2.5

Questions on the patients’ sociodemographic characteristics concerned their age, sex, marital status, level of education, and occupation type (Table 1). Quality of life is measured using the Chinese version of the WHOQOL-BREF questionnaire. The WHOQOL-BREF consists of 26 items, scored on a 5-point Likert scale of 1 to 5, with an item score of 1 indicating “not at all” or “very poor/dissatisfied” and an item score of 5 indicating “very good,” “completely,” or “extremely.” There are 2 general items regarding health conditions which would be analyzed independently. The other items evaluate quality of life (QOL) in 4 main domains: physical health (7 items), psychological (6 items), social relationships (3 items), and environment (8 items). Three items are phased negatively and hence, scored in reverse. The domain scores are computed separately and the raw score of each domain is converted into a 0 to 100 transformed score, according to the WHOQOL user manual. After conversion, the maximal scores for the physical health, psychological, social relationships, and environment domains are 100 respectively, with a higher score indicating a better QOL. Satisfactory reliability and validity of WHOQOL-BREF have been demonstrated in the Chinese population with a Cronbach-a coefficient of 0.892.

**Table 1 T1:** Patient baseline demographics.

Demographics	Combined group	Music group	Tai Chi group	*P* value
Number of patients				
Age^∗^ (y)				
Male sex (no. [%])				
BMI^∗^ (kg/m^2^)				
Follow-up^∗^ (mo)				

BMI = body mass index.

∗ The values are given as the mean and the SD.

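### Two-group tests at an unadjusted P < .05 do not fit a three-arm trial with six separately analysed scores, and they inflate the chance of a false-positive finding

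*Protocol article*

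**What the plan says.** Section 2.3 (Random allocation) sets up a three-arm design: "Eligible participants are divided into 3 groups according to completely randomized design", namely combined, music alone and Tai Chi alone.

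Section 2.5 (Outcomes) describes the WHOQOL-BREF. For the four domains, "The domain scores are computed separately". On the rest, "There are 2 general items regarding health conditions which would be analyzed independently". That makes six scores, and none is called primary.

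Section 2.6 (Statistical analysis) names two methods for comparing continuous data. The independent t test "will be used in case of normally distributed data", with Mann–Whitney U otherwise. It then states that P < .05 "will be considered significant for all analyses". It names no three-group test.

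The Introduction and Discussion ask whether the combination is more effective than treatment alone, and whether there is synergy.

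**The concern.** Each of the two named tests compares two groups. Neither can compare three arms in one step, so the plan can only be carried out as a set of separate pairwise tests, repeated for every score. The article's own Table 1 shows the mismatch: it has one P value column across three groups, and neither named test can fill that column for a continuous row such as age or BMI.

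Two things are at stake. First, a flat .05 applied to every test does not hold the overall error rate at 5%. Second, there are two single-therapy comparators. If the combination were no better than one of them, but both were better than the other, a win over the weaker arm would become likely as the sample grows. Nothing in the text stops that win from being reported as the combination beating single treatment.

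**Working it through.** **Inputs from the article.** Three arms (section 2.3); 4 + 2 = 6 scores (section 2.5); .05 per test (section 2.6). The article states no overall error rate, sample size or between-score correlation, so there is no figure of its own to reproduce.

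**Assumptions.** Tests are two-sided, arms are equal in size, there is no true difference on any score, large-sample z tests are used, and the six scores share a common correlation ρ.

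**Number of tests.** All three pairs: 3 × 6 = 18. Only combined versus each single therapy: 2 × 6 = 12.

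**Simple formula.** If all tests were independent, the chance of at least one P < .05 would be 1 − 0.95^18 = 0.603 or 1 − 0.95^12 = 0.460. These figures are too high: pairs that share an arm cannot be independent, even when ρ = 0.

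**Simulation.** Draw each arm's six standardised means with correlation ρ. For each pair and score, form z = (difference of the two arm values)/√2 and compare |z| with 1.96. With 400,000 replicates for the two-directional rates and 200,000 for the directional one:

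| Six scores, no true difference | ρ = 0 | 0.3 | 0.5 | 0.7 | 0.9 |
|---|---|---|---|---|---|
| Any P < .05, three pairs (18 tests) | 54% | 50% | 44% | 35% | 24% |
| Any P < .05, two combined-versus-single pairs (12 tests) | 43% | 40% | 35% | 28% | 19% |
| Any P < .05 favouring the combination over either single therapy | – | 21% | 18% | 14% | – |

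The benchmark for the third row is .05/2 = 2.5%, the error in one direction of a single two-sided .05 test.

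**One score only.** Any of three pairs: about 12%. Either combined-versus-single pair, in either direction: about 9%. The combination beating at least one single therapy: about 4.5%, half of the 9%.

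**The both-must-win rule.** Suppose the combination is truly no better than one of the single therapies. To claim superiority, the test against that therapy must wrongly come out significant in the combination's favour, which happens at most 2.5% of the time. Requiring the second win as well can only lower this. No splitting of alpha is needed.

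**The case against.** The strongest objection is that this is a condensed article. The choice of contrasts, their order and any multiplicity procedure commonly sit in a statistical analysis plan, so their absence is no fault. That stands as far as it goes: silence about contrasts is not the finding. But the article is not silent on the tests or the threshold. It names two-group tests for a three-arm trial and applies .05 to everything. An analysis plan with a joint model or an adjustment would depart from this text.

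Several stronger readings are also open to challenge, and here the objection is right:

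- A reader might take 35–50% as the chance of falsely claiming that the combination is better. It is not. It includes music versus Tai Chi and results where the combination is worse. The directional figure is 14–21%.
- A reader might take the 9% for one score as the combination beating either therapy. That rate is about 4.5%; the 9% counts both directions.
- A reader might quote 60% for uncorrelated scores. Because pairs share arms, the figure is 54%.
- A reader might infer that any one significant test of 18 would count as success. The article gives a per-test threshold and no rule for declaring success, and testing two pairs is as consistent with the text as testing three.
- A reader might infer that the article requires the combination to beat both components. That is a sensible reading of its question, but it is not stated.

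**Conclusion.** The concern holds in a conditional form. Section 2.6 fixes tests and a threshold that do not match the three-arm, six-score design, and following them inflates false positives on every reading checked. For any nominally significant difference over the six scores, the rate is about 35–50% with three pairs (24–54% for ρ from 0.9 down to 0), or 28–40% with two pairs (19–43%). For a false result favouring the combination over either single therapy, it is about 14–21% at ρ of 0.3 to 0.7.

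These sizes rest on no true difference on any score, equal arms and a common correlation. None of them comes from the article, so the figures should be quoted with those assumptions. They cover only the six WHOQOL-BREF scores at one time point. The lack of any safeguard against reporting a win over one component as a win over single treatment does not depend on the correlation.

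**What to change.** Replace the two-group tests in section 2.6 with a three-arm analysis:

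- **Model.** A linear model with arm as a factor. For non-normal scores and the two 5-point items, use Kruskal–Wallis with pairwise rank tests, or an ordinal model.
- **Primary claim.** The sponsor names one primary outcome before unblinding. The combination is called better only if it beats music alone and Tai Chi alone on that outcome, each at two-sided .05.
- **Remaining domain scores.** Apply the same both-must-win rule. Take the larger of the two P values for each domain and Holm-adjust across those domains. If the primary outcome is itself a domain, it is left out of this set.
- **Everything else.** Music versus Tai Chi and the two general items are reported descriptively, and the sentence applying .05 to all analyses is removed.

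The cost is fewer nominally significant findings and less power than either contrast has alone. The analysis text is easy to change, but choosing a primary outcome is a design decision that the sponsor has to make and keep.

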## Discussion

3

Depression is a common health problem and an increasing global burden. WHO has found unipolar depression to be the third largest burden of disease globally in 2004 and is projected to rank first in 2030. A result of depression is the loss of social and cognitive functions and quality of life. One of the symptoms in depression is reduction in sleep quality (insomnia). Sleep disturbances associated with depression include difficulties in falling asleep and maintaining sleep.^[11]^ Cognitive behavioral therapy is recommended in clinical guidelines as first-line treatment. Other treatment modalities for sleep promotion include sleep hygiene, physical activity, light therapy, relaxation techniques, music/nature sounds, and acupuncture. Resolving sleep disturbances in patients with active or previous depression is important as it may prevent worsening of symptoms and relapse of depression.^[12]^

However, it is still controversial whether combined music and Tai Chi therapy will be more effective than treatment alone for patients with major depression. Based on the separate effectiveness of Tai Chi and music mentioned above, we combined Tai Chi with soft relaxing Chinese folk music, to determine whether a synergistic effect would be present in the control of depressive symptoms among community-dwelling persons in China. Therefore, the primary objective of the present study was to evaluate the efficacy of Tai Chi and music therapy on psychological status and quality of life among patients with major depressive disorder in China.
